### Instruments and Measures

Because this is a fully naturalistic study, we will use only instruments and measures that are routinely applied at the KGI to all patients. That is, to avoid methodological artifacts such as design or experimenter effects, we will not add additional assessment procedures that are not part of the basic psychotherapy evaluation. In consequence, the coverage and range of assessment instruments is limited those applied at the study site. However, note that there are further instruments applied at the KGI that are not considered in the present study, because they are administered only to selected patients with specific problems or because they were considered redundant for the present study aims. Normal-range personality will be assessed with a German adaptation (99) of the well-established Big Five Inventory (BFI) (100). The BFI is a brief self-report inventory capturing the basic structure of personality based on the broad domains of neuroticism, extraversion, openness, conscientiousness, and agreeableness. The BFI has been validated in diverse samples across nations, including English, German, Dutch, and Chinese, and is considered a reliable and valid short assessment of the FFM (99–102). Personality will be further assessed using the German adaptation (103) of the Inventory of Interpersonal Problems (IIP) (104). The IIP relies on the interpersonal circumplex model (105, 106) and captures personality difficulties based on the following eight primary domains of interpersonal problems, that is, domineering, vindictive, cold, socially avoidant, submissive, exploitable, overly nurturant, and intrusive. On a higher-order level, these domains collapse into the meta-factors of agency/dominance and communion/affiliation. The circumplex personality domains revealed strong and consistent associations with both the Big Five traits of extraversion and agreeableness and personality disorder dimensions (107–109), which is why personality pathology is considered a disorder of interpersonal behavior (110–112). In addition to the self-report IIP, an informant rating scale of the circumplex model will also be administered using the Impact Message Inventory-Circumplex (IMI-C) (113, 114). The informant rating will be provided by various sources; however, in most cases, the rater will be the partner/spouse or a family member. The BFI will be assessed at both baseline and 6-month follow-up, while IIP and IMI-C will be completed at baseline only due to their length.

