(1)BFI traits show high differential continuity over time (all *r* > 0.6). To test this prediction, we will compute bivariate Pearson correlations between trait scores at baseline and 6-month follow-up. We will provide both attenuated and disattenuated correlation coefficients corrected for scale unreliability.(2)BFI traits demonstrate substantial mean-level continuity (all *d* < 0.5). More specifically, we predict that only neuroticism will demonstrate modest mean-level change (0.2 < *d* > 0.5), while the other four traits will remain almost unaltered over time (all *d* < 0.2). These predictions will be tested with *t*-tests for paired samples by examining the differences in standardized mean-level change between baseline and 6-month follow-up.(3)Baseline BFI traits, specifically high neuroticism and low conscientiousness, substantially reduce (*d* > 0.5) the effectiveness of psychotherapy based on the BSI, GAF, and INK over the 6-month observation period. In order to test this prediction, we will compute GEE (121). These statistical models were introduced to fit regression analyses that account for within-subject correlation, which is an inherent part of longitudinal studies that rely on repeated outcome measures. Together with mixed models and random coefficient models, GEE represent the state of the art for longitudinal data analysis and are preferred to repeated measures ANOVA due to their superior psychometric properties (122, 123). The baseline BFI traits will be entered as the predictor variables and the repeated measures of the BSI, GAF, and INK successively as the outcome. The effect size of interest will be modeled as the interaction term between baseline personality and the time slope coefficient of the repeated outcomes, that is, the linear time trend for change in BSI, GAF, and INK. By simultaneously adjusting for the intercept, such a statistical modeling ensures that change in psychopathology over time is estimated independent of baseline impairment. These models will be conducted with and without adjustment for baseline diagnoses based on ICD-10.(4)Mean-level change in BFI traits is only weakly, if at all, correlated with change in psychopathological impairment over time (all *r* < 0.3). To test this hypothesis, we will compute individual change scores over time for all repeated measures by subtracting the baseline score from the follow-up score. The change scores of the BFI traits will then be correlated with the change scores of the BSI, GAF, and INK using Pearson correlation.

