
Second paper: the second confirmatory analysis will focus on the IIP and IMI-C. We will test the following hypotheses:
(1)Self-reports and informant ratings of interpersonal personality problems are only modestly correlated (all *r* < 0.3). To test this hypothesis, we will subject the IIP (self-report) and the IMI-C (informant rating) to a bivariate Pearson correlation analysis.(2)Both self-reported and informant-rated baseline personality problems according to the IIP and IMI-C substantially reduce (*d* > 0.5) the effectiveness of psychotherapy according to change in BSI, GAF, and INK from baseline to 6-month follow-up. As specified above with respect to the BFI, we will test these predictions by focusing on the interaction effect between baseline personality measures and the time slope coefficients of the psychopathology outcomes using a series of GEE analyses.(3)Self-other agreement in personality profiles relates stronger to the outcome of psychotherapy than either self-report (IIP) or informant rating (IMI-C). To test this hypothesis, we will first compute the index of profile agreement (*I*_pa_) between IIP and IMI-C as recommended by McCrae (124) and then compare the slope-interaction effect of the *I*_pa_ with the multivariable effects obtained for the IIP and the IMI-C domains based on the results of GEE as specified above. The difference between two effect sizes will be considered statistically significant if the 95% confidence intervals of their standardized regression coefficients do not overlap.(4)IIP and IMI-C have substantial incremental criterion validity (Δ*R*^2^ > 0.05) above and beyond each other in the prediction of the outcome of psychotherapy. This hypothesis will be tested by subjecting the change scores over time for BSI, GAF, and INK to a hierarchical linear regression analysis, where baseline IIP and IMI-C are entered in interchangeable hierarchical blocks as the predictor variables. In these models, the effect size of interest will be the amount of additional variance explained (Δ*R*^2^) accounted for by either IIP or IMI-C in the prediction of intraindividual change in BSI, GAF, and INK over time.

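### Second paper, hypothesis 3: one agreement-index coefficient is compared with mutually adjusted domain coefficients, so an instrument-level claim is not tested like for like

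*Protocol article*

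**What the plan says.** All references are to the protocol article.

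- **Claim.** Under Hypotheses and Planned Analyses, second paper, hypothesis 3 says that self-other agreement in personality profiles "relates stronger to the outcome of psychotherapy than either self-report (IIP) or informant rating (IMI-C"). Both comparators are named as whole instruments.
- **Test.** The slope interaction of a single profile agreement index is compared "with the multivariable effects obtained for the IIP and the IMI-C domains based on the results of GEE as specified above". A difference counts as significant when the two 95% confidence intervals of the standardized coefficients do not overlap.
- **Models referred to.** Hypothesis 2 examines personality-by-time interactions "using a series of GEE analyses", following the first paper's models, where "The baseline BFI traits will be entered as the predictor variables". Neither sentence says whether the predictors share one model.
- **Structure of the instrument.** Under Instruments and Measures, the IIP "captures personality difficulties based on the following eight primary domains of interpersonal problems", and "these domains collapse into the meta-factors of agency/dominance and communion/affiliation". Hypotheses 2 and 3 name neither a total score nor the meta-factors.
- **Hypothesis 4.** It enters the IIP and the IMI-C as blocks and judges them by the change in R². The agreement index is not part of it.

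**The concern.** Hypothesis 3 asks whether agreement outperforms an instrument. Its test asks whether agreement outperforms what is left of single domains after the other domains have been held constant. These are different questions. Mutual adjustment removes what the domains have in common, and a general level of interpersonal problems would show up as exactly that common part. The index faces no such adjustment.

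The text also gives no rule for weighing one coefficient against eight, or against 16 if the IMI-C is also scored on eight domains. It does not say whether the index must exceed one domain, the average domain or every domain, nor whether signs are disregarded. The article's stated aim is to reduce analytic flexibility, and a comparison with several readings leaves the conclusion on hypothesis 3 to be chosen after the results are seen.

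**Working it through.** **Inputs from the article.** Eight IIP domains; expected effect d > 0.5 in hypothesis 2; about 100 six-month follow-ups; α = 0.05 (taken as two-sided); two measurement times. With two times and complete data, the predictor-by-time GEE coefficient equals the regression coefficient on the change score. The article gives no figure for the hypothesis 3 comparison, so there is none to reproduce, and n = 100 is taken as given.

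**Assumptions, not in the article.** Inter-domain correlation ρ, equal for all pairs and varied from 0 to 0.7; an effect carried equally by the domains; an agreement index independent of the domains.

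**1. Effect on the correlation scale.** r = d/√(d² + 4) = 0.5/√4.25 = 0.243.

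**2. Division of the effect.** With k = 8:
- mutually adjusted coefficient per domain = r/√(k(1 + (k − 1)ρ)) = 0.243/√(8 + 56ρ)
- VIF = (1 + 6ρ)/((1 − ρ)(1 + 7ρ))
- SE = √(VIF(1 − r²)/(n − k − 1)), with n − k − 1 = 91

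At ρ = 0.4: coefficient 0.243/√30.4 = 0.044; VIF = 3.4/(0.6 × 3.8) = 1.49; SE = √(1.49 × 0.941/91) = 0.124.

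| ρ | coefficient per domain | share of 0.243 | SE | power per domain |
|---|---|---|---|---|
| 0 | 0.086 | 35% | 0.102 | 14% |
| 0.2 | 0.055 | 23% | 0.109 | 8% |
| 0.4 | 0.044 | 18% | 0.124 | 6% |
| 0.6 | 0.038 | 16% | 0.151 | 6% |
| 0.7 | 0.035 | 15% | 0.174 | 6% |

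A single IIP score keeps 0.243, with power of about 68 to 70% at n = 100. Entered one at a time, each domain would show 0.243 × √((1 + 7ρ)/8), which runs from 0.086 at ρ = 0 to 0.208 at ρ = 0.7.

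**3. Point estimates in the comparison (simulation, n = 100).**
- True r = 0.35 for the IIP and 0.20 for the index, ρ from 0.26 to 0.47: the index exceeds the average absolute domain coefficient in about 81% of studies, the largest domain coefficient in 32 to 37%, and the IIP total in about 13%.
- Both equal at 0.243, ρ from 0.2 to 0.6: the index exceeds a given domain in 87 to 90% of comparisons, and the single score in about 50%.

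**4. The article's own rule, non-overlap of 95% intervals.**
- Scenario 0.35 against 0.20, absolute coefficients: 0.1 to 0.3% per domain, at most about 1% for any of eight, 0% for all eight.
- Same scenario, signed coefficients: about 3% per domain, 15 to 18% for any of eight, 0% for all eight.
- Equal effects, signed: 5 to 6% per domain and about 30% for at least one of eight, against 0.2 to 0.3% for a single score. On absolute values the any-of-eight figure falls to about 1.4%.

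**The case against.** **The formal rule does not favour the index.** This is the strongest objection, and it stands. A reader might infer from the 81% that the study would declare agreement superior. That figure compares point estimates with an average the plan never computes. Adjusted intervals are wide, and on absolute coefficients non-overlap is almost never reached. The roughly 30% at equal strength needs signed coefficients and a reading in which any one domain suffices, so sign handling and multiplicity produce most of it, not the division of the effect.

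**Hypothesis 2.** A reader might also infer that hypothesis 2 would be rejected even if overall problem severity had the predicted effect. The text does not support that. Multivariable domain effects are mentioned only in hypothesis 3; hypothesis 2 speaks of a series of models and is compatible with one model per measure or with a total score. The concern reaches it only if the domains are entered jointly.

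**Domain analysis is legitimate.** The circumplex describes distinct problem areas, and an effect specific to one domain would stay in that domain's coefficient instead of being divided. This limits the size of the problem, but hypothesis 3 is still worded for whole instruments.

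**Hypothesis 4 covers the instrument level.** It does so for the IIP and the IMI-C against each other, but without the agreement index, so it leaves hypothesis 3 uncovered.

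**The article is condensed.** A fuller protocol may define the scores. The mismatch, however, lies in a comparison the article itself states.

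**Conclusion.** The concern holds for hypothesis 3 of the second paper. The stated comparison is not like for like and cannot show whether agreement relates more strongly to outcome than either instrument. Where problem level is shared across eight domains, each adjusted coefficient carries about 15 to 35% of the instrument's effect for ρ from 0.7 to 0. Point estimates then lean towards the index even when the instrument is the stronger predictor. The formal rule is close to uninformative on absolute coefficients, and its result on signed coefficients depends on which reading is chosen.

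The direction of the point-estimate tilt is the same over the whole assumed range of ρ. Its size rests on correlations the article does not give and on an effect spread equally across domains. The documents do not establish that agreement would be formally declared superior, nor that hypothesis 2 would fail. The point should be corrected, but it affects one hypothesis and not the whole analysis.

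**What to change.** For hypothesis 3, represent each instrument by one prespecified effect. Two options fit:

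- **One score per instrument:** the IIP mean over its eight domains and one overall IMI-C summary. A dominance or affiliation axis score would not serve as the summary, because it describes interpersonal style and not the level of problems.
- **A block-level R²,** as in hypothesis 4. Use adjusted or cross-validated R², since eight predictors unrelated to outcome have an expected raw R² of about 8/99 = 0.08 at n = 100.

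Compare this effect with the agreement index on the same absolute metric, using a direct test or a bootstrap confidence interval for the difference in place of interval overlap. Report domain coefficients as secondary. State for hypothesis 2 whether domains are entered jointly, singly or as a score.

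The cost is wording only; every measure is already planned, and only six follow-ups were complete at the time of writing. The downside is that domain-specific effects become secondary in hypothesis 3.

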Collection of data will include all German-speaking patients between 18 and 65 years who started psychotherapy at the KGI in Zurich dating back to September 2015 when FFM measures of personality were included in the standard test battery. Even though therapy is also offered to English speaking patients, restriction to German-speaking patients was made because assessments in English comprise different questionnaires. Data from a comprehensive assessment at outset of the psychotherapy will be used as baseline measures. After 6 months, all patients will be reassessed with a subset of these measures unless their therapy ended prior to that. These data will be used as the 6-month follow-up assessment. Originally, we planned to reassess patients after 12 months (second follow-up), but we now came to realize that this is not feasible because there are not enough patients who remain incessantly in therapy for so long. The 12-month follow-up will therefore not be executed. Based on power analyses, we intend to proceed sampling until we have approximately *n* = 100 6-month follow-up assessments. Because sample size calculation is intricate and not readily applicable for generalised estimating equations (GEE) analysis, we relied on the following three sources: firstly, we scrutinized various sample size recommendations for correlated data published in the methodological literature (84–86); secondly, we tested different sample size estimations based on repeated measure ANOVA calculated with G*Power (87); and thirdly, we considered the significance levels for varying effect sizes as obtained from applications of GEE in our previous work (14, 88–90). The final sample size of *n* = 100 was then estimated based on all these sources for an expected moderate effect size (0.3 < *d* > 0.5), a significance level of α = 0.05 and power (1 − β) > 0.8.

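### Second paper, hypothesis 3: the CI non-overlap rule is not a 5% test of a difference, and on signed coefficients it can call equally strong effects different

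*Protocol article*

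**What the plan says.** All references are to the protocol article.

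- Under Hypotheses and Planned Analyses, second paper, hypothesis 3 reads "Self-other agreement in personality profiles relates stronger to the outcome of psychotherapy than either self-report (IIP) or informant rating (IMI-C"). This is a directional claim about strength.
- To test it, the authors compute an index of profile agreement from the IIP and the IMI-C. They then "compare the slope-interaction effect of the" index with the multivariable effects of the IIP and IMI-C domains from the GEE models.
- The decision rule is "The difference between two effect sizes will be considered statistically significant if the 95% confidence intervals of their standardized regression coefficients do not overlap". The article does not mention absolute values, sign alignment or the covariance between the estimates.
- Hypothesis 2 of the same paper gives a direction for the problem scores: "Both self-reported and informant-rated baseline personality problems according to the IIP and IMI-C substantially reduce" the effectiveness of therapy. No direction is given for the agreement index.
- Under Instruments and Measures, the IIP has "eight primary domains of interpersonal problems".
- Under Study Site and Sampling Procedure, "we intend to proceed sampling until we have approximately" 100 six-month follow-ups, for "a significance level of α = 0.05 and power (1 − β) > 0.8". That is the only significance level in the article.

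**The concern.** Two separate things are wrong with the rule, and they act in different directions.

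First, two 95% intervals can overlap while the difference between the estimates is clearly significant at 5%. Non-overlap is therefore a much stricter criterion than a test of the difference. How much stricter depends on the correlation between the two estimates. The index is built from the same two questionnaires in the same patients, so that correlation cannot be presumed to be zero, and the rule does not use it. At stake is power, in a study of about 100 patients.

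Second, the claim is that one predictor relates more strongly than another, which is a comparison of magnitudes. The rule compares coefficients with their signs. A coefficient of +0.30 and one of -0.30 are equally strong but lie far apart, and their intervals can separate for that reason alone. At stake is a positive finding on a confirmatory hypothesis when there is no difference in strength.

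**Working it through.** **Inputs.** From the article: the rule, alpha 0.05 (two-sided assumed) and about 100 follow-ups. Assumed, because the article does not give them: the correlation rho between the two estimates (range -0.5 to 0.5) and the standard error (SE) of a standardized coefficient (0.10, about 1/sqrt(100); 0.15 also tried).

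**The plan's own figure.** No size or power is stated for this comparison. The 100 follow-ups agree with a paired change at d = 0.3: n = ((1.96 + 0.84)/0.3)^2, about 88 (90 by the t distribution), with power 0.84 at n = 100. That calculation says nothing about comparing two coefficients.

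**Size and power of the rule.** Non-overlap means |b1 - b2| > 1.96 (SE1 + SE2). In SEs of the difference the cut is

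z = 1.96 (SE1 + SE2) / sqrt(SE1^2 + SE2^2 - 2 rho SE1 SE2),

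which for equal SEs is 3.92 / sqrt(2(1 - rho)). The size is 2[1 - Phi(z)]. Where a direct 5% test has 80% power, the power of the rule is Phi(1.96 + 0.84 - z).

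| rho (assumed) | cut z | size | power (direct test 0.80) |
|---|---|---|---|
| -0.5 | 2.26 | 0.024 | 0.70 |
| 0 | 2.77 | 0.0056 | 0.51 |
| 0.5 | 3.92 | 0.00009 | 0.13 |

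Unequal SEs change this little: at rho = 0 the size is 0.0085 for an SE ratio of 2 and 0.013 for a ratio of 3. The size reaches 0.05 only at rho = -1 and never exceeds it.

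**Opposite signs, equal strength.** For true coefficients +b and -b with independent estimates,

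P(non-overlap) = 1 - Phi((1.96 (SE1 + SE2) - 2b) / sqrt(SE1^2 + SE2^2)).

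| SEs (assumed) | b | calculation | P(non-overlap) |
|---|---|---|---|
| 0.10, 0.10 | 0.20 | (0.392 - 0.40)/0.141 = -0.06 | 0.52 |
| 0.10, 0.10 | 0.30 | (0.392 - 0.60)/0.141 = -1.47 | 0.93 |
| 0.10, 0.15 | 0.30 | (0.490 - 0.60)/0.180 = -0.61 | 0.73 |
| 0.15, 0.15 | 0.30 | (0.588 - 0.60)/0.212 = -0.06 | 0.52 |

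At SE 0.10 and b = 0.30, letting rho run from -0.3 to 0.3 moves 0.93 only between 0.90 and 0.96.

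Support for the hypothesis also needs the index to have the larger absolute estimate. With opposite signs this depends on b1 + b2, whereas non-overlap depends on b1 - b2. With equal SEs the sum and difference are uncorrelated, so the index looks stronger in half of the non-overlapping samples: 0.523/2 = 0.26 at b = 0.20 and 0.929/2 = 0.46 at b = 0.30.

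**Simulation.** Setting: 100 patients, two standardized predictors of the change score in one joint model, predictor correlation -0.3, 0 or 0.3, 10,000 runs each.

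| True coefficients | non-overlap rule rejects | sign-aligned test with covariance rejects |
|---|---|---|
| +0.3 and +0.3 | 0.2% to 1.7% | 5.1% to 5.5% |
| +0.3 and -0.3 | 90% to 98% | 5.1% to 5.8% |

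Coefficients from separate models were not simulated; that case is covered only by the range over rho above.

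**The case against.** The strongest defence is that the rule is conservative. The authors' declared worry is false positives, the rule is fixed in advance, its size never exceeds 5%, and the article does not itself call it a 5% test. For coefficients of the same sign this stands: the cost is power, not false claims. A reader might infer that the non-overlap criterion in itself inflates the false-positive rate, or that it doubles the required distance from 1.96 to 3.92 SEs of the difference. Neither follows. The figure 3.92 counts SEs of a single coefficient; in SEs of the difference, for independent estimates, the cut is 2.77, a factor of 1.41.

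Conservatism does not answer the sign problem, but the defence limits it in three ways. First, opposite signs are conjecture: the article gives no direction for the index, and sign alignment may be what the authors intend when they speak of a stronger relation. Second, a reader might take 52% and 93% as rates of false confirmation. They are rates of non-overlap; the rates at which the index also looks stronger are 26% and 46%, and requiring it to beat several domains would lower them further. Third, an SE of 0.10 is optimistic for eight mutually adjusted, correlated domains, and larger SEs reduce the effect as shown.

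A reader might also infer that setting one index against mutually adjusted domain coefficients is invalid in itself. No figure was derived for that, and the point does not rest on it.

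**Conclusion.** The concern holds in two parts. The non-overlap rule is not a 5% test of a difference: with equal SEs and independent estimates its size is 0.0056 and its power 0.51 against 0.80 for a direct test, and across an assumed rho of -0.5 to 0.5 the power runs from 0.70 to 0.13. This part follows from the stated rule and depends on assumptions only for its exact size. The second part is conditional. If the index and a problem score have opposite signs, the rule as written can separate equally strong effects and, at the assumed SE of 0.10, make the index look stronger in 26% to 46% of samples for |beta| 0.20 to 0.30. The article does not support saying that this will happen, only that nothing in the rule prevents it.

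Severity: should-fix. The rule decides one of eight confirmatory hypotheses and leaves the design, the sample size and the other hypotheses untouched. The article presents its analyses as exactly prespecified, so this is a rule fixed badly and not a detail left to a fuller plan.

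**What to change.** Replace the overlap sentence with a direct test of the difference in absolute (sign-aligned) standardized slope-interaction coefficients, |beta_index| - |beta_domain|. Use an SE or confidence interval that includes the joint covariance of the two estimates: a joint GEE, stacked models with patient-level robust covariance, or a patient-level bootstrap of that coefficient difference. Conclude that agreement relates more strongly only if the 95% CI of the difference lies above 0. The simulation above supports the calibration of this test at |beta| = 0.30 in a joint model. It did not cover coefficients close to zero, where the sign itself is uncertain, so check that case before the text is fixed.

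Do not substitute a naive bootstrap of adjusted or cross-validated R2 for the index against an eight-domain block. It changes the quantity compared, and it is itself miscalibrated. In check simulations of adjusted R2 at equal strength (100 patients), the bootstrap mean shifted by about -0.06. The index was declared stronger in at most 0.5% of runs against a nominal 2.5%, and the interval lay wholly below 0 in about 12%.

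Cost: a change of wording and a little more analysis, with no new data. The article reports six completed follow-ups at the time of writing, so as of that date the change could be made before results are known.

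### Second paper, hypothesis 4: the only criterion is raw ΔR² above 0.05 with block size unstated; with eight-domain blocks at n = 100, a block with no effect passes about 78% of the time

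*Protocol article*

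**What the plan says.** All references are to the Protocol article. In Hypotheses and Planned Analyses, second paper, hypothesis 4 states that the IIP and IMI-C "have substantial incremental criterion validity (Δ*R*^2^ > 0.05) above and beyond each other" for the outcome of psychotherapy. The test is described as "subjecting the change scores over time for BSI, GAF, and INK to a hierarchical linear regression analysis", in which "baseline IIP and IMI-C are entered in interchangeable hierarchical blocks as the predictor variables". The text adds that "the effect size of interest will be the amount of additional variance explained" by either instrument. It names no F-test of the change, adjusted R², confidence interval or cross-validation for this hypothesis. Hypothesis 3 of the same paper does give a significance rule, based on confidence intervals that do not overlap.

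Hypothesis 4 does not list the scores in a block. Instruments and Measures says that the IIP "captures personality difficulties based on the following eight primary domains of interpersonal problems" and that these collapse into two meta-factors, agency/dominance and communion/affiliation. It describes the IMI-C as an informant scale of the same circumplex model and gives no number of scores. Hypothesis 3 refers to the "multivariable effects obtained for the IIP and the IMI-C domains". The target is about 100 six-month follow-ups (Study Site and Sampling Procedure).

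**The concern.** In-sample R² cannot fall when predictors are added, and it rises with each one even if none is related to the outcome. A fixed cut-off on the raw increase therefore means different things for different block sizes. With one predictor and 100 patients, 0.05 is a demanding bar. With eight predictors it lies below what noise alone produces on average.

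Hypothesis 4 carries much of the study's aim of comparing the predictive validity of self-reports and informant ratings. If domains are entered and the raw value is judged against 0.05, either instrument could be reported as adding substantially to the other on a given outcome when it adds nothing. The choice of scores, which drives this error rate, is left open in a plan whose stated purpose is to close off such flexibility.

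**Working it through.** **Inputs.** The threshold is 0.05 on raw ΔR² (hypothesis 4). There are three outcomes, BSI, GAF and INK; with each instrument tested over the other, that gives 3 × 2 = 6 comparisons. n = 100. The IIP has eight domains (Instruments and Measures). Eight for the IMI-C is an assumption, based on the shared circumplex model.

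**The plan's own figure.** n = 100 is attributed to three sources combined, for a d of roughly 0.3 to 0.5, so no single formula reproduces it. It is compatible with power above 0.8 for within-person change: a two-sided paired t-test at d = 0.3 needs 90 and has power 0.844 at 100. Nothing in that planning is on the ΔR² scale. I take n = 100 as given.

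**Neither instrument predicts outcome.** For k predictors in the added block,

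ΔR² ~ Beta(k/2, (n − 1 − k)/2), with mean k/(n − 1).

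For k = 8, n = 100 this is Beta(4, 45.5), with mean 8/99 = 0.081.

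| Scores per block | Mean ΔR² | 95th percentile | P(ΔR² > 0.05) |
|---|---|---|---|
| 8 | 0.081 | 0.152 | 0.777 |
| 2 | 0.020 | 0.060 | 0.083 |
| 1 | 0.010 | 0.039 | 0.025 |

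With eight scores, a 5% error rate on the raw value would need a cut-off of about 0.15. If the achieved number of follow-ups were 80 or 120, the eight-score probability would be 0.875 or 0.66.

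**First block already explains R₁.** For a useless second block of eight after a first block of eight,

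ΔR² = (1 − R₁) × Beta(8/2, (99 − 16)/2).

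| First-block R² | 0.10 | 0.20 | 0.30 | 0.40 | 0.50 |
|---|---|---|---|---|---|
| P(ΔR² > 0.05) | 0.77 | 0.70 | 0.61 | 0.49 | 0.34 |

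**Joint results.** These come from simulation with 10,000 replicates and eight scores per block, assuming correlations of 0.3 within and between instruments and no true effect. Both instruments pass on a given outcome in about 61% of trials. All six comparisons pass in 23% (outcomes uncorrelated) to 27% (outcome correlation 0.5).

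**What an observed 0.05 is worth.** With first-block R² = 0.08 and ΔR² = 0.05,

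F = (0.05/8) / ((1 − 0.13)/83) = 0.60 on 8 and 83 df, p = 0.78.

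Adjusted R² moves from 1 − 0.92 × 99/91 = −0.001 to 1 − 0.87 × 99/83 = −0.038, a fall of 0.037. It rises only if ΔR² exceeds 0.92 × 8/91 = 0.081.

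**Power of the F-test for a true ΔR² of 0.05.** I use f² = 0.05/(1 − R² of the full model) and noncentrality n·f². For full-model R² of 0.05 to 0.25, f² is 0.053 to 0.067 and the noncentrality 5.3 to 6.7.

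- Eight-score blocks (8 and 83 df): power 0.29 to 0.36.
- Two-score blocks (2 and 95 df): power 0.51 to 0.62.

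The other common convention, f² times (numerator df + denominator df + 1), gives 0.26 to 0.33 and 0.50 to 0.61.

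**The case against.** Four points can be made for the plan.

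**Block size is an inference.** Hypothesis 4 names the instruments, not their domains. The reference to domains is in hypothesis 3, which uses a different analysis (GEE). With two scores per block the problem is mild, and with one it disappears. This stands, and the severe figures must be stated conditionally. Eight domains remains the natural reading: it is how the IIP is described, hypothesis 3 speaks of domains for both instruments, and no total score is named for either.

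**0.05 may be only a predicted effect size.** It is written in the same form as the d and r values in the other hypotheses, α = 0.05 is set for the study, and a test of the change is not excluded. That is fair as far as it goes. But the article gives no other criterion for hypothesis 4, and a raw sample ΔR² is biased upward, so comparing it with 0.05 does not check a prediction about the true value either.

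**The hypothesis is not certain to pass.** A reader might infer that it could hardly fail, or that chance always meets the criterion. The documents do not support that. Read as requiring each instrument to add to the other on all three outcomes, it passes in only about a quarter of null trials. The high rate applies to single comparisons.

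**0.78 is towards the upper end.** Caveats and Potential Pitfalls speaks of holding baseline impairment constant and of primary diagnosis as a covariate. It is unclear whether that covers hypothesis 4. Terms that explain outcome before the block enters would lower the rate, as the table by first-block R² shows.

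**Conclusion.** The concern holds in conditional form. Hypothesis 4 gives raw ΔR² above 0.05 as its only criterion and leaves the predictors per block unstated. If each block holds eight domains and n = 100, the expected ΔR² of a useless block (0.081) is above the threshold. A single comparison then passes by chance with probability about 0.78, or 0.77 down to 0.34 as first-block R² rises from 0.10 to 0.50. Both instruments pass on one outcome in about 61% of null trials, and all six comparisons in about a quarter. With two scores per block the single-comparison rate is 0.08, and with one score 0.03.

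The result rests on eight scores for the IMI-C as well as the IIP, about 100 patients with change scores and, for the joint rates, the assumed correlations. It does not show that the hypothesis is bound to be confirmed. The plan should be corrected before analysis, but the problem is confined to one of eight confirmatory hypotheses.

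**What to change.** In hypothesis 4:

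1. State which scores enter each block, for example the two meta-factors named in Instruments and Measures, or the eight domains, with the number for the IMI-C.
2. Test the R² change with the block F-test at 0.05. In simulation this held its 5% error rate with eight-score blocks.
3. Compare 0.05 with the adjusted or cross-validated ΔR² and report its 95% CI. Do not compare it with the raw value.
4. Say how the six comparisons combine into a conclusion on the hypothesis.

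This takes a few sentences, modest extra computation and no new data. The article reports only six completed follow-ups at the time of writing, so the change could be made then without loss of confirmatory standing.

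The real cost is that low power becomes visible: for a true ΔR² of 0.05 at n = 100, about 0.29 to 0.36 with eight-score blocks and 0.51 to 0.62 with two-score blocks. Two scores per block do better if the meta-factors carry the signal, but they give up domain detail. Either way the plan should say in advance that a non-significant change will not be read as absence of incremental validity, and that the interval will be reported.
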